### Data Management and Monitoring

2.12

All study data will be managed in accordance with a standardized Manual of Operations and Case Report Forms (CRFs) to ensure uniformity in recruitment, assessment, data entry, and confidentiality. Staff will be trained in Good Clinical Practice, with hard copy data stored securely in locked cabinets and identifiers kept separately, while electronic data will be maintained in a secure database at the Biomedical Engineering Department, Jashore University of Science and Technology, accessible only to the principal investigator and authorized research staff. Any use of secondary data will require approval from the Data Management Committee. Monitoring will be conducted by two independent personnel not involved in the intervention, who will oversee participant enrollment, protocol adherence, adverse events, and interim analyses. Any necessary modifications to the study design or intervention will be promptly reported to the Ethical Review Board by the principal investigator.

### Data Analysis

2.13

All analyses will be conducted by an independent statistician using SPSS version 22 with anonymized, encrypted data. Data will be screened for completeness, missing values, and outliers prior to analysis. Normality will be assessed using the Kolmogorov–Smirnov and Shapiro–Wilk tests, along with measures of skewness and kurtosis, and visual inspection (histograms and *Q*–*Q* plots). Descriptive statistics will be presented as mean ± standard deviation for normally distributed variables, median (interquartile range) for non‐normally distributed variables, and frequency (percentage) for categorical variables. Baseline characteristics (e.g., age, BMI, disease duration) will be compared between the two groups to assess group equivalence. Given the two‐group design (intervention vs control) with four time points (baseline, mid‐intervention, post‐intervention, and follow‐up), a two‐way repeated‐measures ANOVA (group × time) will be used for normally distributed outcomes to evaluate main effects and interaction effects. For non‐normally distributed data, the Friedman test (within‐group) and Mann–Whitney *U* test (between‐group at each time point) will be applied, with appropriate post hoc analyses. Within‐group changes over time will be assessed using repeated‐measures ANOVA (or Friedman test), while between‐group differences at each time point will be examined using independent *t*‐tests (or Mann–Whitney *U* tests). When significant interactions are identified, post hoc pairwise comparisons with appropriate corrections (e.g., Bonferroni) will be performed. Effect sizes (e.g., partial eta squared or Cohen's *d*) and mean differences with 95% confidence intervals will be reported alongside p‐values. All tests will be two‐tailed, with statistical significance set at *p* < 0.05. An intention‐to‐treat (ITT) approach will be applied, and missing data will be handled using the last observation carried forward (LOCF) method. Additionally, change scores across all four time points will be calculated to support the interpretation of clinical relevance.

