Despite the widespread use of FES in neurorehabilitation, current evidence regarding its effectiveness in reducing hand pain and improving function in people with stroke remains inconclusive. Several studies have reported improvements in motor performance following FES application; however, considerable variability in intervention protocols, outcome measures, and study populations limits the generalizability of the findings. Moreover, pain is a significant yet often underreported barrier to functional recovery and has not been adequately addressed in most of the FES‐focused trials. Notably, few randomized controlled trials (RCTs) have concurrently examined both pain and hand‐specific functional outcomes following FES in individuals with stroke [21]. Although recent literature encourages the use of FES in upper extremity stroke rehabilitation, its application, especially when combined with well‐structured standard care for post‐stroke hand impairments, remains limited and still unfamiliar in clinical settings. Previous studies have shown mixed results, often hindered by poor methodology, limited outcome measures, and a lack of long‐term follow‐up, leaving their optimal effectiveness uncertain when assessed with robust methodological standards [13, 18].

Therefore, this prospective, randomized controlled trial (RCT) is relevant and aims to complement and contribute to the existing scientific effort by maintaining a strong methodological rigor. The primary objective of this trial is to evaluate the effectiveness of FES‐integrated UPT in reducing hand pain and improving hand function in stroke patients. The secondary objectives are: (1) to evaluate sociodemographic factors such as age, gender, stroke type, and time since stroke that may affect post‐stroke pain and functional recovery; (2) to establish baseline compatibility between the experimental and control groups; (3) to assess changes and compare group differences across all outcome measures at mid and post‐intervention periods; and (4) to explore the long‐term benefits of FES‐integrated UPT in maintaining improvements during the follow‐up period. It is hypothesized that FES‐integrated UPT will result in significantly greater improvements in hand pain, function, muscle tone, and manual dexterity compared to placebo FES with UPT, with these improvements being more long‐lasting.

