### Sample Size Calculation

2.3

Sample size calculation is performed using G*Power software version 3.1.9.7 for a two‐tailed independent‐groups test comparing two group means. The effect size (Cohen's *d*) is set to 0.5 (medium effect) based on prior research in post‐stroke rehabilitation [23]. The α value is predetermined as 0.05, and the power (1–β) is 0.80 to limit the risk of Type II error. Based on these parameters, we will need 64 individuals per group, for a total of 128 participants. Finally, we plan to recruit 140 participants (70 per group), allowing for an anticipated dropout rate of approximately 10%.

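### Baseline is analysed as an outcome and never adjusted for, and a data-driven normality switch picks the test: adjusting for baseline would gain power at no cost in data or patients

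*Protocol article*

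**What the plan says.** All of the analysis wording is in section 2.13 (Data Analysis) of the protocol article.

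- **Parametric route.** Baseline, week 4, week 8 and week 20 are the four levels of a two-way repeated-measures model: "ANOVA (group × time) will be used for normally distributed outcomes to evaluate main effects and interaction effects". Independent t-tests compare the arms at each visit. No baseline covariate is named.
- **Rank route.** Outcomes judged non-normal get the Friedman test within each arm and the Mann–Whitney test between arms at each visit.
- **Choice of route.** It depends on Kolmogorov–Smirnov and Shapiro–Wilk tests, "along with measures of skewness and kurtosis, and visual inspection".
- **Within-arm tests.** Within-group "changes over time will be assessed using" repeated-measures ANOVA or Friedman.
- **Change scores.** They are calculated to help interpret clinical relevance. No between-arm test of them is named.

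The Introduction hypothesises that FES with usual physiotherapy "will result in significantly greater improvements in hand pain, function, muscle tone, and manual dexterity compared to placebo FES with UPT". Section 2.3 sizes the trial for a two-group comparison of means. It names no visit, no outcome and no covariate.

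**The concern.** Three features pull the analysis away from the stated hypothesis.

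1. **Baseline as an outcome level.** Randomised arms have no expected difference at baseline. Entering it as a fourth level makes the interaction a 3-degree-of-freedom omnibus test, and the baseline value is not used to reduce the variance of any between-arm comparison. The per-visit t-tests and Mann–Whitney tests ignore baseline altogether.
2. **A route chosen after looking at the data.** The switch examines the distribution of the outcome, whereas a linear model's assumption concerns residuals. The article's own facts make the rank route likely for three of the four outcomes. NPRS is an 11-point scale with no minimum pain at entry. MAS is ordinal and limited to 1 to 2 in the wrist flexors at entry. BBT counts blocks moved by patients at Brunnstrom stage 3 or less. On that route no test is baseline-adjusted or compares change between arms.
3. **Within-arm p-values.** Friedman and within-arm ANOVA compare no arms. Patients enter 1 to 3 months after stroke and all receive physiotherapy, so both arms may improve, and these tests do not bear on the comparative hypothesis.

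At stake is power that could be had from a measurement already planned, and a primary result whose form is not known until the data are inspected.

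**Working it through.** **Inputs from the article**

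- Section 2.3: "The α value is predetermined as 0.05"; power "is 0.80 to limit the risk of Type II error"; Cohen's d "is set to 0.5 (medium effect) based on prior research in post‐stroke rehabilitation"; 64 per group.
- Section 2.13: "All tests will be two‐tailed, with statistical significance set at" p < 0.05.

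**Assumed, because the article does not give them:** the correlation ρ between visits (equal for all pairs, 0.3 to 0.7) and the pattern of effect over the visits.

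**Step 1. Reproduce the plan's figure.** For a two-sample t-test the noncentrality (F scale) is (n/2)·d² = 32 × 0.25 = 8 on 1 and 126 df. Power is 0.801, and the exact requirement is 63.8, so 64 per group. The stated size reproduces, but for one unadjusted comparison of means.

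**Step 2. Same comparison, adjusted for baseline (ANCOVA).** Residual variance is multiplied by 1 − ρ², so the noncentrality is 8/(1 − ρ²) on 1 and 125 df.

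| ρ | 1 − ρ² | Noncentrality | ANCOVA power | Unadjusted t-test |
|---|---|---|---|---|
| 0.3 | 0.91 | 8.79 | 0.84 | 0.80 |
| 0.5 | 0.75 | 10.67 | 0.90 | 0.80 |
| 0.7 | 0.51 | 15.69 | 0.98 | 0.80 |

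**Step 3. The planned group × time interaction.** The noncentrality is (n/2)·Σ(δ − mean δ)²/(1 − ρ) on 3 and 378 df, where δ is the standardised arm difference at baseline and weeks 4, 8 and 20.

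- Effect peaking at week 8, δ = (0, 0.25, 0.5, 0.25): mean 0.25, sum of squares 0.125.
- Constant effect, δ = (0, 0.5, 0.5, 0.5): mean 0.375, sum of squares 0.1875.

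| ρ | Peaking: noncentrality, power | Constant: noncentrality, power | Week-8 ANCOVA |
|---|---|---|---|
| 0.5 | 32 × 0.125/0.5 = 8.0, 0.65 | 32 × 0.1875/0.5 = 12.0, 0.84 | 0.90 |
| 0.7 | 32 × 0.125/0.3 = 13.3, 0.88 | 32 × 0.1875/0.3 = 20.0, 0.97 | 0.98 |

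The interaction is well below ANCOVA when the effect is not constant. It is about equal when the effect is constant and ρ is 0.7 or more.

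**Step 4. The rank route on a scale with a floor.** A 0–10 outcome was simulated (latent mean 2, SD 2.5, shift of 0.5 SD, rounded and cut at 0 and 10; all assumed), with 64 per arm and 3,000 trials per setting.

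| ρ (latent) | Mann–Whitney, week 8 | ANCOVA | Rank ANCOVA |
|---|---|---|---|
| 0.5 | 0.74 | 0.82 | 0.82 |
| 0.7 | 0.73 | 0.93 | 0.93 |
| 0.8 | 0.75 | 0.98 | 0.98 |

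Shapiro–Wilk rejected in every trial. With no treatment effect, all three methods rejected in 5.1% to 5.4% of trials. So the unadjusted rank test is valid, the adjusted methods are equally valid, and adjustment adds 8 to 23 percentage points.

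**The case against.** The strongest reply is that nothing here is invalid, and that is right. A reader might infer several stronger things that the article does not support.

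- **That the hypothesis goes untested on the rank route.** It does not. Randomised arms share one baseline distribution, so a Mann–Whitney test at a later visit is a valid test of the treatment effect.
- **That the week-8 difference was the powered comparison.** Section 2.3 names no visit, and section 2.8 lists four time points without marking one as primary. Week 8 in the working is an illustration.
- **That the diluted group main effect is the efficacy test.** Section 2.13 does not single it out. Post hoc comparisons follow a significant interaction, and the interaction does test differential change.
- **That the planned ANOVA always loses power.** This depends on ρ and the effect pattern. For a constant effect with ρ of 0.7 or more the loss is negligible.
- **That the rank route rules out the promised mean differences and confidence intervals.** They can be reported beside a Mann–Whitney p-value.
- **That a normality test alone decides the route.** Skewness, kurtosis and plots also count. That leaves room for judgement, but the choice is still made from the trial's data.

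A separate analysis plan may exist. That does not answer the point, because the article states these methods outright and does not leave them open. What remains is that no between-arm analysis adjusts for baseline, that the rank route has no test of change, and that the route is not fixed in advance.

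**Conclusion.** The point holds as a free improvement, not as an error that threatens the trial's validity. The between-arm tests at each visit keep their type I error, but they leave unused a baseline value that the trial already collects. For one comparison at d = 0.5 with 64 per arm, adjustment raises power from 80% to about 84%, 90% or 98% at ρ of 0.3, 0.5 or 0.7. The planned interaction has 65% (ρ 0.5) to 88% (ρ 0.7) if the effect peaks at week 8, and roughly matches the adjusted comparison if the effect is constant and ρ is at least 0.7.

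These sizes rest on assumed correlations and effect patterns, equal correlation between visits, and approximately normal residuals. The floored-scale figures rest on one assumed distribution; actual NPRS, MAS and BBT data may behave differently. That these three will take the rank route is probable, not certain. The direction of the single-visit comparison depends little on these choices: adjustment beat the unadjusted test at every correlation examined.

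**What to change.** In section 2.13:

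1. For each primary outcome (NPRS and FMA-UE), prespecify one baseline-adjusted comparison between arms at one named visit. Use ANCOVA, or a mixed model on weeks 4, 8 and 20 with baseline as covariate. The result is the adjusted mean difference with its 95% confidence interval.
2. For the ordinal or floor-prone secondary scales (MAS, BBT), name in advance a baseline-adjusted ordinal or rank analysis. The exact model is a matter of preference; fixing it beforehand is what counts.
3. Delete the switch between parametric and rank methods based on the observed distribution.
4. Report within-arm changes descriptively, without p-values.

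If the mixed model is chosen, bring the sentence on last observation carried forward into line with it, since such a model can use the observed visits directly.

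The cost is a change of wording and slightly more modelling work. No extra data or participants are needed, and section 2.16 says that recruitment has not begun.

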### Outcome Measurements

2.8

The primary outcome measures will focus on hand pain and function, with hand pain measured using the Numeric Pain Rating Scale (NPRS) and hand function using the Fugl‐Meyer Assessment for Upper Extremity (FMA‐UE). Secondary outcomes will include muscle tone and manual dexterity, with muscle tone measured using the MAS and manual dexterity using the Box and Block Test (BBT). Spasticity will specifically be evaluated in the wrist flexors, finger flexors, and elbow flexors of the affected limb, as these muscle groups are commonly associated with post‐stroke upper extremity spasticity patterns. Individual participant sociodemographic information related to stroke will also be collected at baseline assessment. The primary and secondary outcomes will be measured at four time points: baseline, mid‐intervention (week 4), post‐intervention (week 8), and 12‐week follow‐up (week 20).

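### Two primary outcomes at three post-baseline times have no primary time point or success rule, so the stated 5% error and 80% power do not hold together for the trial's claim

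*Protocol article*

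**What the plan says.** Section 2.8 and the abstract name two primary outcomes, NPRS and FMA-UE, without ranking them or stating how many must succeed. On timing, section 2.8 says "The primary and secondary outcomes will be measured at four time points": baseline and weeks 4, 8 and 20. None is singled out. The Introduction places the week 4 and week 8 comparisons under a secondary objective, "to assess changes and compare group differences across all outcome measures at mid and post"-intervention, and follow-up under a further secondary, exploratory one.

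Section 2.13 plans a group × time repeated-measures ANOVA with main and interaction effects, and names no term as primary. It then says that between-group "differences at each time point will be examined using independent" t-tests or Mann-Whitney tests. All tests are two-"tailed, with statistical significance set at" p < 0.05. Bonferroni appears as an example of a correction for pairwise comparisons after a significant interaction. The non-normal branch goes straight to Mann-Whitney tests at each time, with post hoc analyses that are not specified.

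Section 2.3 sizes the trial for one comparison of two means with d = 0.5: "The α value is predetermined as 0.05", power "is 0.80 to limit the risk of Type II error", and "we will need 64 individuals per group, for a total of 128 participants". It ties this to no outcome or time point. In section 2.12, two independent monitors are people "who will oversee participant enrollment, protocol adherence, adverse events, and interim analyses"; nothing more is said about the interim analyses.

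**The concern.** Error rate and power belong to a claim, and the protocol does not define the claim. With two primary outcomes, three post-baseline times and one 0.05 threshold, success could be declared on whichever result is significant, and the chance of a false claim then exceeds 5%. If both outcomes are meant to succeed, the error rate is protected, but the sample size for a single test no longer gives 80% power. The choice between these readings would be made after the data are seen. Section 2.16 says that nobody has yet been recruited, so it can still be settled in advance.

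**Working it through.** **Inputs.** From section 2.3: d = 0.5, two-sided α = 0.05, power 0.80, 64 evaluable per arm. From section 2.8: 2 primary outcomes × 3 post-baseline times = 6 between-group tests. The protocol gives no correlations. Assumed ranges are 0 to 0.9 between times and 0 to 0.7 between outcomes for the error rate, and 0 to 0.5 between outcomes for joint power.

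**1. The plan's own figure.** The two-sample t-test (noncentral t) needs 63.77, rounded up to 64 per arm, with power 80.1% at 64. The figure reproduces, for one test.

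**2. Any one result suffices.** For k independent tests at 0.05, the chance of at least one false positive is 1 − 0.95^k.

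- Two interaction tests, one per outcome: 1 − 0.95² = 9.75%. Simulating the ANOVA with 64 per arm gave 9.2% to 9.9%.
- Six per-time tests, independent: 1 − 0.95⁶ = 26.5%.
- Six per-time tests, correlated (simulated z-tests, 400,000 draws):

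| Correlation between times | Correlation between outcomes | At least one false positive |
|---|---|---|
| 0.5 | 0 | 23.5% |
| 0.7 | 0.3 | 20.1% |
| 0.8 | 0.3 | 18.2% |
| 0.9 | 0.7 | 13.5% |

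The six-test range is therefore about 14% to 26%.

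**3. Both outcomes must succeed at one time, each at 0.05.** The error rate is not inflated. Power at d = 0.5 for each outcome with 64 per arm is 0.8015² = 64.2% if the outcomes are independent, and 68.9% by simulated t-tests if they correlate at 0.5. For 80% joint power, independent outcomes need √0.80 = 0.894 each, about 84 per arm.

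**4. Alpha split equally over two outcomes at one time.** At 0.025 each, power with 64 per arm is 71.2%. With 77 per arm it is 79.8% and with 78 it is 80.4%, so 78 are needed: 156 evaluable, and 156 / 0.90 = 173.3, so 174 recruited against the planned 140.

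**5. Interim analyses, only if they test efficacy.** One unadjusted look at half the data would raise a single 0.05 test to 8.4%. This is not part of the ranges above.

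**The case against.** The strongest reply is that section 2.13 puts the group × time ANOVA first, as the analysis fitted to the design, and does plan corrections. The Introduction treats the per-time comparisons as secondary. If the interaction test of each primary outcome is what counts, the family is two tests and the error is about 10%. If per-time tests were allowed only after a significant interaction and were Bonferroni-corrected over three times, the error from those tests would be about 1% to 2%. The text does not settle whether the per-time t-tests and the corrected post hoc comparisons are the same tests.

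This stands as a limit on size. It does not remove the problem. No ANOVA term is named primary, the two outcomes share no alpha rule, the non-normal branch has no interaction gate, and about 10% is still twice the nominal level.

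A reader might infer that the type I error is about 20%. The documents do not support a single figure: 20% needs all six tests to count as primary, each sufficient alone and uncorrected, with assumed correlations near 0.7 over time. A reader might also count success at an interim look. Section 2.12 does not say that these analyses compare the arms on efficacy, so any contribution is conditional.

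A statistical analysis plan may exist and could hold interim boundaries. But this article itself fixes two primaries, the tests, the 0.05 threshold and a one-test sample size, so the core cannot be left to a document not shown.

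**Conclusion.** The point holds as a mismatch between the claim, the tests and the sample size. Under an either-outcome rule, the false-positive chance is about 10% (two interaction tests) or about 14% to 26% (six per-time tests). Under a both-outcomes rule at one time, the error is controlled but power is about 64% to 69%. Splitting alpha equally gives 71%. None of these delivers 5% error and 80% power together with 64 per arm. The figures rest on the protocol's d = 0.5, applied to each outcome in the power calculations, and on the assumed correlations. Confidence is high that the primary comparison and success rule are undefined; the size depends on which reading the sponsor intends.

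**What to change.** Before recruitment, amend the protocol and the registry entry:

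- **Sections 2.8 and 2.13:** name one primary time point, for example week 8, one between-group contrast, and a success rule for the two primary outcomes. A fixed sequence is one option: for example, FMA-UE at two-sided 0.05, then NPRS at 0.05 only if FMA-UE is significant. The order is the sponsor's choice, since the title and objective give pain and function equal standing. Make the other time points, MAS and BBT secondary, either Holm-adjusted or reported as estimates with 95% confidence intervals.
- **Section 2.3:** state that 80% power applies only to the comparison tested first, and give the power for the rest.
- **Section 2.12:** state that the interim analyses involve no between-arm efficacy testing, or give their alpha boundary.

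**Cost.** The fixed sequence needs only wording and no extra participants. Its downside is that the second outcome can be claimed only after the first, with about 64% to 69% power to claim both. The alternatives cost participants: 78 evaluable per arm for an equal alpha split, or about 84 per arm for 80% power that both succeed if the outcomes are independent.

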#### Inclusion Criteria

2.6.1

Participants must meet all of the following to be eligible for the study: (1) Confirm diagnosis of unilateral ischemic stroke verified by CT or magnetic resonance imaging (MRI) by a neurologist [24]; (2) Age between 40 and 70 years; (3) Stable vital signs with normal levels of consciousness; (4) Brunnstrom recovery stage between 3 or less for the affected upper extremity function [25, 26]; (5) Presence of mild‐to‐moderate spasticity in the affected upper extremity, based on Modified Ashworth Scale (MAS) score of 1 to 2 in the wrist flexor muscles; (6) Stroke onset between 1 and 3 months before enrollment [27]; (7) Willingness and ability to provide informed consent to participate in the study.

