### Safety Measures and Adverse Effects Management

2.14

Although major side effects are unlikely, participants will be closely monitored throughout the intervention. Any adverse events (e.g., seizure, skin burn) will result in immediate discontinuation of FES and will be reported to the ethics board within 24 h. Participants will be informed of potential mild side effects such as pain, skin irritation, or discomfort, and advised to report them promptly. A history of epilepsy or seizures will be screened prior to FES application. Any serious adverse events or protocol modifications will be documented and submitted to the Institutional Review Board. Safety outcomes will be included in the final trial report to ensure comprehensive risk–benefit evaluation.

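### LOCF is the only missing-data method, in a trial where scores are expected to keep changing and lasting benefit at week 20 is a hypothesis

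*Protocol article*

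**What the plan says.** All of this is in the protocol article.

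- **Method (2.13 Data Analysis).** "An intention‐to‐treat (ITT) approach will be applied", and "missing data will be handled using the last observation carried forward (LOCF) method". No other missing-data method is given. The completed data go into a group × time repeated-measures ANOVA, with t-tests at each visit, or into rank tests if non-normal.
- **Population (2.6.1 Inclusion Criteria).** "Stroke onset between 1 and 3 months before enrollment".
- **Treatment (2.7).** Both arms receive usual physiotherapy three times a week for 8 weeks, with active or placebo FES.
- **Visits (2.8).** Baseline and weeks 4, 8 and 20. The last visit is 12 weeks after treatment ends.
- **Aims (Introduction).** The fourth secondary objective is to explore the benefit of FES in "maintaining improvements during the follow‐up period". The hypothesis is greater improvement than control, "with these improvements being more long‐lasting".
- **Dropout (2.3).** About 10% is anticipated.

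**The concern.** LOCF is unbiased only in special circumstances, chiefly when scores do not change after the last visit attended. The article does not say outright that patients keep recovering. It follows from entry at 1 to 3 months, from active therapy in both arms, and from a hypothesis that requires scores to move.

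Three things follow.

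1. A participant who leaves before week 4 is analysed at every later visit with the baseline score. One who leaves before week 8 is analysed with the week-4 score.
2. A participant lost after week 8 has the week-8 score entered at week 20. For that person, persistence of benefit is imputed, not observed, although persistence is what the week-20 visit is meant to test.
3. Carried-forward values enter the ANOVA and t-tests as if measured, so the uncertainty of the imputation is ignored.

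At stake are the treatment effect on both primary outcomes and the reading of week 20.

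**Working it through.** **The plan's own figure.** Section 2.3 uses an effect that "is set to 0.5 (medium effect) based on prior research in post‐stroke rehabilitation", two-sided alpha 0.05 and power 0.80. The exact t-test gives 64 per arm (power 0.801), as stated. Recruiting 140 for 128 evaluable allows 1 − 128/140 = 8.6% loss, close to the stated 10%. The sample size is not in dispute.

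**Check 1: week-8 effect on FMA-UE.** None of these inputs is in the article; all are assumptions.

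- Control gain is 10 points by week 8, with 60% of it (6 points) by week 4.
- The true FES effect is 5 points at week 8 and 2.5 at week 4, so FES gains are 15 and 8.5. Five points equals the planned 0.5 SD if the SD is 10.
- Half of dropouts leave before week 4 (frozen at baseline, gain 0), and half before week 8 (frozen at week 4).

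For dropout share d, the LOCF mean gain in an arm is (1 − d) × gain8 + d × (0.5 × 0 + 0.5 × gain4).

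| Scenario | FES arm | Control arm | LOCF effect | True effect |
|---|---|---|---|---|
| 10% in both arms | 0.90×15 + 0.10×4.25 = 13.925 | 0.90×10 + 0.10×3 = 9.30 | 4.62 | 5 |
| 15% FES, 5% control | 0.85×15 + 0.15×4.25 = 13.3875 | 0.95×10 + 0.05×3 = 9.65 | 3.74 | 5 |
| 5% FES, 15% control, no effect | 0.95×10 + 0.05×3 = 9.65 | 0.85×10 + 0.15×3 = 8.95 | +0.70 | 0 |

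The first row is about 8% too small (0.375/5) and the second about 25% too small (1.2625/5). Swapping the dropout rates in the third row gives −0.70, so the sign follows whichever arm loses more people.

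**Check 2: week-20 effect.** If a share m of each arm is lost after week 8, the LOCF effect at week 20 is (1 − m) × D20 + m × D8, where D8 and D20 are the true effects in SD units. Assume D8 = 0.5 and full waning, D20 = 0. The result is then 0.5m. The chance of a significant two-sided t-test with 70 per arm uses noncentrality effect × √(70/2) on 138 degrees of freedom.

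| Missing at week 20 | LOCF effect (truth 0) | Chance of p < 0.05 |
|---|---|---|
| 10% | +0.05 SD | 6.0% |
| 20% | +0.10 SD | 9.0% |
| 30% | +0.15 SD | 14.3% |

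**Where the bias vanishes.** If D20 = D8 = 0.5 and equal losses occur only after week 8, the formula returns 0.5. With no effect at any visit and equal dropout at equal times, the two arm means are equal and the LOCF effect is 0.

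**The case against.** The strongest reply is that little happens if dropout is as planned. At a balanced 10%, LOCF gives 4.6 instead of 5, which errs towards no effect. At week 20 it adds at most about 0.05 SD under full waning, with 6% rejection instead of 5%. This is fair, and it limits the size of the point. It does not rescue the method, because the 10% is only anticipated, balance cannot be guaranteed, and the direction is not reliably conservative. Durability is also an exploratory secondary objective, but it appears in the hypothesis too.

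A reader might infer more than the article supports, in three ways.

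- **That LOCF builds in the week-20 result.** It imputes durability only for participants whose week-20 value is missing, about a tenth of the trial if the plan holds.
- **That adverse events will make FES lose more data.** Section 2.14 says that an adverse event "will result in immediate discontinuation of FES and will be reported to the ethics board within 24 h". That stops stimulation, not assessment, and the analysis is by intention to treat. The same section calls major side effects unlikely. Unequal dropout is therefore a scenario, not something the article predicts.
- **That unequal dropout produces false positives for FES.** If FES loses more people while both arms recover, LOCF pulls the FES mean down and spurious findings mostly favour control. They favour FES only if control loses more.

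Two further limits stand. The FMA-UE figures say nothing about the size of any bias on NPRS, the other primary outcome. A Gaussian model also does not suit ordinal MAS. Sensitivity analyses may be specified in an analysis plan not shown, so their absence from the article is not part of this point.

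**Conclusion.** The point holds in limited form. LOCF as the sole method is a poor choice that the article itself fixes, and no other section corrects it. The size depends on assumed recovery and on the timing and balance of dropout. It ranges from no bias, through about 8% attenuation at a balanced 10%, to about 25% attenuation at 15% against 5%. With no true effect, a spurious 0.7 FMA-UE points arises in favour of the arm that loses fewer people. For durability, a fully waned effect leaves a false +0.05 SD at 10% missing and +0.15 SD at 30%. These figures illustrate the mechanism and do not predict this trial's result.

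**What to change.** Replace the LOCF sentence in 2.13, and adapt the ANOVA and t-test wording for the outcomes concerned.

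- **FMA-UE, and NPRS and BBT where approximately normal:** a likelihood-based mixed model for repeated measures using all observed visits of every randomised participant, analysed as randomised. Include arm, visit, arm × visit and baseline × visit, with unstructured covariance. MIXED in SPSS 22, the software already named, fits it. The model assumes data missing at random. With baseline as a covariate, anyone without a later visit contributes no outcome, so report how many there are.
- **MAS and clearly non-normal outcomes:** multiple imputation or an ordinal longitudinal model.
- **Data collection:** state that scheduled assessments continue in participants who stop FES.
- **LOCF:** at most a sensitivity analysis.

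The cost is revised wording and a little more analysis work. Section 2.16 says that no one has been recruited, so the change can be made before any data exist.
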